### Participants

Participants will be people with PD receiving care as outpatients in the designated centres, over the age of 18 years, in any stage of the disease (as determined by a researcher with the Hoehn & Yahr scale [22]), residing at that time in Navarra, fluent in the speaking and understanding of the Spanish language, and with preserved cognitive ability (as determined by medical history or the doctor responsible).

Family members/carers will be over the age of 18, living or maintaining a close relationship with the patient and actively collaborating in his/her care, currently residing in Navarra and fluent in the speaking and understanding of the Spanish language.

Individuals with PD may enter the research project even though they do not have a family carer or the carer does not wish to participate. The family carer will also be able to enter the research project even though the individual with PD cannot participate for not meeting the inclusion criteria or for lack of interest.

Any change in participants’ circumstances during the study which mean that they do not meet the inclusion criteria mentioned above will cause the discontinuation of the participants in the study.

### Sample size

For the quantitative data collection, the sample size necessary to detect medium to large differences in the primary outcome of the project, quality of life, was calculated. To this end, a previous study of the ReNACE programme [11] with patients with PD and family carers was taken as a reference point together with previous studies [13, 23], using the quality of life scales that will be used in this study in people with PD and family carers. Furthermore, previous research on patients [19, 24] and family carers [25] has been taken into account to calculate the percentage of losses expected during follow-up. Calculation of the sample size was performed using the statistical programme STATA for both control and intervention groups. The parameters used for the calculation of the sample size are shown in Table 2.

**Table 2 Tab2:** Parameters used for the calculation of the sample size by group

	Mean (SD) Quality of life	Size effect. Clinically significant difference	Power	Expected losses over follow-up	Ideal sample size
Patients	29.03 (15.44)^a^	10	80%	25%	52
Carers	104.70 (25.04)^b^	15	80%	20%	53

SD: standard deviation

^a^Questionnaire on Parkinson’s disease PDQ-39 of Peto et al. (1995) [26]

^b^Scale of Quality of Life of Care-givers SQLC of Glozman et al. (1998) [31]

The minimum sample size calculated is 52 patients and 53 family carers for the intervention group and the same for the control group. Therefore, the study will require a minimum of 104 patients with PD and 106 family carers.

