### Setting

The study will be carried out in several urban areas of Navarra, in the North of Spain. Specifically, the six health centres in a community setting with the largest numbers of people diagnosed with PD will be chosen in order to maximise the recruitment of participants and improve the power of the study. At the end of the recruitment of participants, ANOVA and χ^2^ tests will be performed to explore the sociodemographic characteristics of the participants from the intervention group and the control group. In the case of finding a significant difference in a sociodemographic variable, the statistics analyses will adjust by propensity-score analysis or the most suitable statistical technique.

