### Procedure

There will be two groups in this study. Participants in group A will receive the ReNACE psychoeducational intervention while the participants in group B, belonging to the control group, will be given a general educational programme.

Allocation will be made according to the centre in which participants are attended. The experimental intervention was assigned to the centres in a random draw by tossing a coin (heads-control, tails-experimental) [27]. In this study individual randomisation, that is by patient or family carer, is not feasible because there is a high risk of contamination between intervention and control groups when participants interact with each other during their visits to their health centre. This is due to the patients from each health centre usually have the same family physician and nurse, and live in the same neighborhood. We decided to choose the six health centres with the highest numbers of people diagnosed with PD. With this proposed allocation strategy it is expected that contamination between the control and intervention groups will be minimal.

Furthermore, participants will be blinded to intervention assignment [28] as they will only be aware of the intervention they are receiving and they will not know if they belong to the intervention or control group. The healthcare professionals helping the participants in data collection will also be blinded to intervention assignment [28]. The healthcare professionals delivering the sessions to all the participants in the control and intervention groups will always be the same.

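### Table 2's 80% power is an individual-level figure; with allocation by six centres it is not shown to hold and probably falls short in a valid comparison

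*Protocol article*

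**What the plan says.** The Sample size section says that "the sample size necessary to detect medium to large differences in the primary outcome of the project, quality of life, was calculated". Table 2, headed "Parameters used for the calculation of the sample size by group", lists mean and SD, the clinically significant difference, power, expected losses and the resulting size. For patients these are SD 15.44, difference 10, power 80%, losses 25% and 52 per group. For carers they are SD 25.04, difference 15, power 80%, losses 20% and 53 per group. The text below the table confirms it: "The minimum sample size calculated is 52 patients and 53 family carers for the intervention group and the same for the control group". The table has no ICC, no design effect and no number of centres, and alpha is not stated.

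Under Setting, "the six health centres in a community setting with the largest numbers of people diagnosed with PD will be chosen", with improved power given as one reason. Under Procedure, "Allocation will be made according to the centre in which participants are attended", using a coin draw. The same section explains that patients of one centre usually share a physician, a nurse and a neighbourhood.

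The Data analysis section plans unpaired t tests at each time point and a mixed ANOVA of group (two levels) by time (three levels). Neither contains a term for centre.

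**The concern.** When whole centres are allocated, participants in one centre are not independent replicates of the comparison between arms. Two things then reduce power: the variance of the arm difference is multiplied by a design effect, and the between-arm test has only as many degrees of freedom as the number of centres allows. The document itself gives reasons to expect some correlation within centres.

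If Table 2 ignores this, the 80% describes a different design from the one being run. Readers will use that figure to judge what the trial could have detected. They will also use it to judge how far a significant result can be trusted, because an individual-level test of centre-allocated data does not hold its nominal error rate.

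**Working it through.** **Inputs.** From Table 2: patients δ = 10, SD = 15.44, loss 25%, n = 52; carers δ = 15, SD = 25.04, loss 20%, n = 53. From Setting and Procedure: six centres, allocation by centre. Assumed because not stated: two-sided alpha 0.05, three equal-sized centres per arm, ICC 0.01/0.02/0.05.

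**Step 1: reproduce Table 2.** Normal approximation: n = 2(1.96 + 0.842)² SD²/δ².
- Patients: 37.4, so 38 per group. The t-test version needs 39, and 39/0.75 = 52, an exact match.
- Carers: 43.7, so 44 per group. Multiplying, 44 × 1.20 = 52.8, gives the stated 53. Dividing by 1 − loss, 44/0.80, gives 55. The t-test version needs 45, and 45/0.80 = 56.25, so 57.
- One-sided alpha gives 40 and 44, which does not match.

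The figures are therefore individual-level and leave no room for a design effect.

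**Step 2: evaluable numbers.** Patients: 52 × 0.75 = 39 per arm, or 13 per centre. Carers: 53 × 0.80 = 42.4, taken as 42 per arm, or 14 per centre.

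**Step 3: power on raw scores.** Design effect DE = 1 + (m − 1) × ICC. Noncentrality = δ / [SD × √(2 × DE / n)]. Power is taken from the noncentral t with 2n − 2 df (design effect alone) or 6 − 2 = 4 df (centre-level test).

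| | ICC | DE | Design effect alone | 4 df |
|---|---|---|---|---|
| Patients | 0 | 1.00 | 81% | 58% |
| | 0.01 | 1.12 | 76% | 54% |
| | 0.02 | 1.24 | 72% | 50% |
| | 0.05 | 1.60 | 61% | 41% |
| Carers | 0 | 1.00 | 77% | 55% |
| | 0.01 | 1.13 | 72% | 50% |
| | 0.02 | 1.26 | 68% | 46% |
| | 0.05 | 1.65 | 56% | 37% |

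Example, patients at ICC 0.02: 10 / [15.44 × √(2 × 1.24/39)] = 10/3.894 = 2.57.

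**Step 4: detectable difference on 4 df.** 80% power needs a noncentrality of 3.76. For patients this means 3.76 × 3.894 = 14.6 points at ICC 0.02, and 3.76 × 15.44 × √(2 × 1.60/39) = 16.6 at ICC 0.05, against the planned 10.

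**Step 5: baseline adjustment.** The residual SD becomes SD × √(1 − r²), with r the assumed baseline–follow-up correlation. Patients on 4 df: about 67% at r = 0.6, ICC 0.02; about 80% at r = 0.7, ICC 0.01; about 66% at r = 0.7, ICC 0.05. Carers on 4 df at r = 0.7: about 77% at ICC 0.01 and 62% at ICC 0.05.

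**Step 6: the planned test without a centre term.** Its type I error is about 2 × [1 − Φ(1.96/√DE)]. For patients this is 6.4/7.8/12.1% at ICC 0.01/0.02/0.05, and for carers 6.5/8.1/12.7%. At a true 10-point difference the unadjusted patient t test rejects about 79/78/75% of the time.

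**The case against.** The strongest reply is that raw follow-up scores are the wrong yardstick. The primary outcome is defined as improvement relative to the change in controls, and baseline is one level of the mixed ANOVA, so some gain from baseline is built into the plan. That stands in part. A reader might infer that six centres cannot deliver 80%, and the documents do not support so firm a claim. With r = 0.7 and ICC 0.01, patients reach about 80% even on 4 df. If only the design effect is charged, r = 0.5 gives patients about 88/84/74% at ICC 0.01/0.02/0.05 (normal approximation). But the document gives neither r nor ICC, and Table 2 claims no gain from baseline.

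A second reply is that the 4-df figures describe a test that is not planned. This also stands. A reader might infer that the planned analysis would often miss a 10-point effect, but the last step of the working shows that it would not. Its main fault is false positives. That does not rescue the 80%, because power obtained by exceeding the nominal error rate is not power at the 5% level.

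A third point concerns the coin. A reader might infer one independent toss per centre, which would give a 3:3 split with probability 20/64 = 31%. The Procedure section does not say that each centre had its own toss, and tossing within pairs or until one arm was full would give 3:3. The realised split is simply not reported.

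Finally, the carer shortfall is not all due to clustering. At ICC 0 carers already have about 77%, because 53 less 20% leaves only 42.

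**Conclusion.** The concern holds in this form: Table 2's 80% rests on an individual-level calculation and is not shown to apply to a design allocated by six centres. For a valid cluster-level comparison it probably falls short. On raw scores the shortfall for patients runs from a few points (76% at ICC 0.01, design effect alone) to about half the stated power (41% at ICC 0.05, 4 df). With strong baseline correlation and a small ICC it can close.

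These figures rest on an assumed ICC range, assumed correlations, two-sided alpha 0.05 and three equal-sized centres per arm, none of which the document states. The individual-level origin of the patient figure rests only on the assumed alpha. Calling the study quasi-experimental does not remove the clustering. The Limitations section mentions baseline differences between centres but not the effect of centre allocation on power or error rate.

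**What to change.** Keep 52 and 53 per group, and restate Table 2 and the accompanying text with:
- the realised number of centres per arm, and alpha with its sidedness;
- an assumed ICC range (for example 0.01 to 0.05) and the resulting design effect;
- the power or detectable difference for an analysis that accounts for centre and adjusts for baseline, with the assumed correlation shown.

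Describe that same analysis in the Data analysis section, so that the restated figure belongs to a test the protocol contains and type I error is controlled. Mark the present 80% as holding for patients only, under individual allocation with ICC 0. Correct the carer figure separately for the way losses were applied.

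The cost is a less favourable stated figure and a revised analysis paragraph. No extra participants are needed.

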**Methods:**

This quasi-experimental study with control group and mixed methods was designed to evaluate a multidisciplinary psychoeducational intervention. Based on the study power calculations, 100 people with Parkinson’s disease and 100 family carers will be recruited and assigned to two groups. The intervention group will receive the ReNACE psychoeducational intervention. The control group will be given a general educational programme. The study will be carried out in six community-based health centres. The results obtained from the two groups will be collected for evaluation at three time points: at baseline, immediately after the intervention and at 6 months post-intervention. The results will be measured with these instruments: the Quality of Life Scale PDQ-39 for patients and the Scale of Quality of Life of Care-givers SQLC for family carers, and for all participants the Psychosocial Adjustment to Illness scale and the Brief COPE Inventory. Focus groups will be organised with some patients and family carers who will have received the ReNACE psychoeducational intervention and also with the healthcare professionals involved in its development.

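### The Abstract's 100 patients and 100 carers fall below the 104 and 106 that the Sample size section calls the minimum, and 53 carers per group give about 78% power rather than the stated 80%

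*Protocol article*

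**What the plan says.** **Sample size section.** The planning values are all placed in one table: "The parameters used for the calculation of the sample size are shown in Table 2". Its two rows read, in the order mean (SD), difference, power, losses, number per group:

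- "Patients 29.03 (15.44)^a^ 10 80% 25% 52"
- "Carers 104.70 (25.04)^b^ 15 80% 20% 53"

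The text then gives the result per group, "The minimum sample size calculated is 52 patients and 53 family carers for the intervention group and the same for the control group", and the totals: "Therefore, the study will require a minimum of 104 patients with PD and 106 family carers". It names Stata as the software. It gives no alpha, no sidedness, no formula for the loss correction, and no choice between a normal and a t calculation.

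**Recruitment section.** Consecutive sampling continues until the calculated minimum is reached, with a pointer back to the Sample size section.

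**Abstract, Methods.** "Based on the study power calculations, 100 people with Parkinson’s disease and 100 family carers will be recruited and assigned to two groups".

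**Data analysis section.** The group comparisons use unpaired t tests and a mixed factorial ANOVA.

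**The concern.** Two things do not fit together.

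First, the Abstract presents 100 and 100 as the outcome of the power calculation, without a word such as approximately, while the body of the article reports a larger number from that calculation and calls it a minimum. Both statements cannot be right.

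Second, the two rows of Table 2 behave differently when their losses are taken off. The patient row leaves enough evaluable participants for 80% power; the carer row does not. Carer quality of life is part of the primary outcome, so the power stated for it should be the power that the number gives.

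**Working it through.** **Inputs.** From Table 2: patients, difference 10, SD 15.44, power 80%, losses 25%, stated 52 per group; carers, difference 15, SD 25.04, power 80%, losses 20%, stated 53 per group. Allocation is 1:1. Assumption: two-sided alpha 0.05. Participants are treated as independent, since Table 2 lists no clustering parameter.

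**Step 1: evaluable number per group.** Normal approximation: n = 2 × (1.96 + 0.8416)² × SD² / difference².

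- Patients: 2 × 7.849 × 15.44² / 10² = 37.42, so 38. The t-test solution is 38.41, so 39.
- Carers: 2 × 7.849 × 25.04² / 15² = 43.74, so 44. The t-test solution is 44.73, so 45.

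**Step 2: reproduce the stated numbers under each loss rule.**

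| Base calculation and loss rule | Patients (stated 52) | Carers (stated 53) |
|---|---|---|
| normal, n / (1 − loss) | 38 / 0.75 = 50.7, so 51 | 44 / 0.80 = 55 |
| t test, n / (1 − loss) | 39 / 0.75 = 52 | 45 / 0.80 = 56.25, so 57 |
| normal, n × (1 + loss) | 38 × 1.25 = 47.5, so 48 | 44 × 1.20 = 52.8, so 53 |
| t test, n × (1 + loss) | 39 × 1.25 = 48.75, so 49 | 45 × 1.20 = 54 |

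No single line returns both 52 and 53. The first line comes within 2 of each. If the t solution is not rounded before the division, carers need 44.73 / 0.80 = 55.9, so 56. A one-sided 5% test gives only 38–42 patients and 42–45 carers, so it does not explain the table.

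**Step 3: power that the stated numbers give after losses.** Normal approximation: power = Φ(difference / (SD × √(2/m)) − 1.96), with m evaluable per group. The t figures use the noncentral t distribution.

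- Patients, 52 × 0.75 = 39: 81.6% (normal), 80.6% (t). The stated 80% is met.
- Carers, 53 × 0.80 = 42.4: 15 / (25.04 × √(2/42.4)) = 2.758; 2.758 − 1.96 = 0.798; power 78.8% (normal), 77.8% (t). Rounding to 42 gives 78.4% and 77.4%; rounding to 43 gives 79.3% and 78.4%.
- Fifty-three carers would meet 80% only if losses were at most 1 − 44/53 = 17.0% (normal) or 1 − 45/53 = 15.1% (t), against the 20% stated.

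**Step 4: the Abstract's totals, 50 per group.**

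- Against the minimum: 100/104 is 3.8% low for patients; 100/106 is 5.7% low for carers.
- Carers, 50 × 0.80 = 40 evaluable: 76.4% (normal), 75.4% (t).
- Patients, 50 × 0.75 = 37.5 evaluable: 80.1% (normal), 79.0% (t). Rounded down to 37: 79.6% and 78.5%.

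**The case against.** The strongest reply is that little of this affects the trial. The Recruitment section points to the Sample size section, so the operative target is 104 and 106, and no recruitment rule relies on the Abstract. The carer gap is 2 to 4 people per group and 1 to 3 points of power, resting on a planning SD and an expected loss that are themselves uncertain. The 53 is also a minimum, not a cap. All of that stands and limits the weight of the point. It does not remove the contradiction between the two totals, nor the fact that 53 less 20% falls short of 80% under both methods.

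Three stronger readings are tempting, and the document does not support them.

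- A reader might infer that carer losses were handled by multiplying by 1.20 instead of dividing by 0.80. The match with 44 × 1.20 is exact after rounding up, but no formula is stated. Matching both rows exactly also needs a t calculation with division for patients and a normal calculation with multiplication for carers. One consistent rule, normal with division, comes close to both. Multiplication is a possible explanation, not an established one.
- A reader might infer that 100 patients would be underpowered. Under the normal approximation without intermediate rounding, 37.42 / 0.75 = 49.9, so 50 per group suffices; by t test the gap is about one point.
- A reader might infer that recruitment will stop at 100 and 100. The Recruitment section says otherwise.

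**Conclusion.** The contradiction between the Abstract and the Sample size section is certain and needs no assumption: 100 and 100 against a minimum of 104 and 106, both attributed to the power calculation.

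The carer row is slightly inconsistent with its own parameters. Its 53 per group gives about 78% power (77–79% across both methods and either rounding of 42.4), not 80%; a consistent loss correction would give 55 (normal) or 57 (t). These figures rest on the assumed two-sided 5% level. The cause of the discrepancy cannot be determined from the article. The patient row holds.

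The point is worth correcting because it concerns the stated recruitment minimum and power for part of the primary outcome, but its size is modest and it does not call the design into question.

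**What to change.** 1. In the Abstract, replace 100 and 100 with 104 patients and 106 carers.
2. In the Sample size section, state alpha and sidedness, say whether a normal or a t calculation was used, and give one loss rule, n / (1 − loss), for both rows of Table 2.
3. Keep 53 carers per group and restate the carer power, after 20% losses, as about 78%. If the sponsor prefers to keep 80% in the table, the matching number is 55 (normal) or 57 (t) per group, that is 110 or 114 carers in total.

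With the power restated, the cost is a few edited lines and no change to design or enrolment. Keeping 80% instead would mean 4 to 8 more carers in total.

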### Recruitment

A consecutive cases sampling will take place in the centres participating in the study until the minimum calculated sample size is achieved (see above).

Given the difficulties involved in the recruitment of this population, different strategies have been planned [26] to reach the required sample size: a) Posters will be put up announcing the study in visible areas in the participating centres; b) Letters will be sent from the centres themselves to the homes of all the people diagnosed with PD who meet the inclusion criteria. The letters will contain information about the study and how to join the study, a stamped addressed envelope and the informed consent form; c) The study will be explained to the professionals of the participating centres in a session. Here they will be encouraged to personally inform the people who come to their consultations about the study; d) In the strategies described above the ReNACE logo will be included, which has been designed to distinguish the study from other information that the target population might receive. Those interested may sign up for the study by telephone, by sending a letter in a stamped addressed envelope (provided by the research team) or in person at the reception of the participating centres. Subsequently, a member of the research team will evaluate if the potential participants meet the inclusion criteria by means of a brief interview in the health centre. Once it has been established that participants fulfill the inclusion criteria, they will be given a document with the dates of the sessions that they must attend and of data collection.

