**Fig. 1 Fig1:**
[figure not shown]
Flow diagram with the design of this study. PD: Parkinson’s Disease

**Table 1 Tab1:** Project Timeline

	Year 1 (2015)			Year 2 (2016)			Year 3 (2017)			Year 4 (2018)		
Task	Q1	Q2	Q3	Q4	Q5	Q6	Q7	Q8	Q9	Q10	Q11	Q12
Random allocation of interventions to participating centres	×											
Dissemination of interventions in participating centres	×	×	×	×	×	×	×	×	×			
Delivery of letters to patients and carers	×		×		×		×		×			
Data collection at baseline (Questionnaire T0)	×		×		×		×		×			
Participants from experimental and control groups receive the intervention at a time	×		×		×		×		×			
Data collection after the intervention (Questionnaire T1)	×		×		×		×		×			
Data collection 6 months post-intervention (Questionnaire T2)			×		×		×		×		×	
Focus groups post-intervention with patients and carers					×	×	×					
Focus group with professionals										×		
Analysis of qualitative data					×	×	×	×	×	×	×	×
Analysis of quantitative data											×	×
Dissemination of findings											×	×

This study is part of the ReNACE research programme aimed at designing multidisciplinary and individualised interventions to promote positive living with a LTC in patients and relatives.

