### Limitations

The non-randomised and voluntary nature of the participation could limit the generalisation of results. However, statistical generalization is not sought in this study but a breakthrough in an area of interventional research that has been neglected for many years when it comes to PD and family carers and illness adjustment. In particular, patients at an advanced stage of PD may not take part in the intervention due to their disability and that young patients who have been diagnosed only recently may not enroll in the intervention due to the stigma of PD being thought of as a disease of the elderly. However, given that centres from different health areas of Navarra will participate, it is expected that the likelihood of this effect influencing the results will be diminished. Similarly, the reliability and sensitivity of the measurement scales that will be used in the study, together with the use of repeated measures, the presence of a control group and the baseline comparison between groups, are all important factors that will help to overcome the limitation mentioned above.

Another limitation could be the baseline differences between the centres selected in the quasi-experiment. However, it is expected that non-statistically significant differences will be found between participants given that the populations of the centres share a similar socio-economic and cultural context.

Furthermore, a limitation of this study is to successfully encourage people with PD and their family carers, who generally do not participate in activities on a regular basis, to attend the intervention each week. It is necessary to bear in mind that given the age and physical condition of the target population the number of subjects lost to the study could be greater than usual in longitudinal studies. However, to minimise this effect, at the end of each session participants will receive a small introduction to the topic of the following week which will help to increase enthusiasm and promote regular attendance.

It is also necessary to point out that in this study it is not possible for the professionals giving the sessions to be blinded, given that there are two different types of intervention. However, researchers involved in the data collection and participants for group A and B will be blinded to the intervention. Also the content and methodology of each session will be established previously in a manual that the professionals will use.

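### People are enrolled after their centre's arm is fixed, by routes that can reveal the programme, so entry and early drop-out can depend on arm; the plan does not name this threat to the comparison.

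*Protocol article*

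**What the plan says.** **Allocation.** The protocol article's Procedure section makes the centre the unit: "Allocation will be made according to the centre in which participants are attended". The draw is described as already done: "The experimental intervention was assigned to the centres in a random draw by tossing a coin". In Table 1 (Project Timeline) the row "Random allocation of interventions to participating centres" is marked in the first period only. Letters, T0 and delivery recur in periods 1, 3, 5, 7 and 9. The row "Dissemination of interventions in participating centres" is marked in every period from 1 to 9.

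**Recruitment.** The Recruitment section lists several channels. One does not depend on staff choice: "Letters will be sent from the centres themselves to the homes of all the people diagnosed with PD who meet the inclusion criteria". Another is a briefing session for centre professionals, after which "they will be encouraged to personally inform the people who come to their consultations about the study". A research team member then holds a short eligibility interview. Once people are found eligible, "they will be given a document with the dates of the sessions that they must attend and of data collection".

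**Programmes.** The intervention has nine weekly 90-minute sessions and the control programme has five.

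**Blinding.** It is stated for participants, in the sense that they do not know which group their programme represents, and for those who collect data. None is stated for the referring professionals or the eligibility interviewer.

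**Limitations.** "The non-randomised and voluntary nature of the participation could limit the generalisation of results". The same section separately accepts that centres may differ at baseline, and expects no significant differences.

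**The concern.** A coin toss over centres protects against bias in which centres get which programme. It does not protect against bias in which people join once the programme at their centre is settled. If those who refer, screen or sign up can respond to the programme, the arms may be filled with different kinds of people.

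Two routes are open here. A professional who knows the local programme may encourage different patients to join. A person who sees nine dates rather than five may withdraw before baseline for reasons linked to prognosis, such as frailty, or the carer's available time. The Limitations section itself says that age and physical condition make regular attendance hard for this population, so a response to programme length is plausible.

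The internal validity of the arm comparison is at stake. The article discusses voluntary entry only as a limit on generalisation.

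**Working it through.** **1. Order of events.** Allocation is in period 1 only and letters go out in periods 1, 3, 5, 7 and 9. At least four of the five waves therefore enrol people into centres whose arm is already fixed. The Procedure section's past tense for the draw suggests the same for the first wave.

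**2. What each step can reveal.**

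| Step | Stated | Inferred |
|---|---|---|
| Staff briefing | Study is explained; staff encouraged to inform patients | Staff may know their centre's programme (Table 1 shows dissemination of the interventions alongside every wave) |
| Cognitive criterion (Participants) | May be judged by the responsible doctor | Local staff can influence eligibility |
| Session list | Given once eligibility is established; shows session and data-collection dates | Probably precedes T0, since it announces data-collection dates |

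The list makes the commitment visible: 9 × 1.5 h = 13.5 h against 5 × 1.5 h = 7.5 h. Not knowing the group label does not hide this. The list gives dates and comes after sign-up, so it would act on drop-out between sign-up and T0 rather than on who is first approached.

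**3. Number analysed.** Inputs from Table 2 for patients: SD 15.44, difference 10, power 80%, losses 25%, 52 per group. Alpha is not stated; I assume 5% two-sided. A t-based calculation gives 38.4, so 39 per group, and 39 / 0.75 = 52. This reproduces the plan's figure. Expected completers are 39 per arm.

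**4. Illustration for an unadjusted t test at T1 or T2.** Assume no true effect and no clustering. The standard error is 15.44 × √(2/39) = 3.50. With 76 degrees of freedom the critical value is 1.99. The noncentrality is the shift divided by the standard error.

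| Assumed selection shift | In SD | Noncentrality | Rejection probability |
|---|---|---|---|
| 0 | 0 | 0 | 5% |
| 3 points | 3/15.44 = 0.19 | 3/3.50 = 0.86 | 13.5% |
| 5 points | 5/15.44 = 0.32 | 5/3.50 = 1.43 | 29.2% |

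The documents give no size for a selection effect. The 3 and 5 points are assumptions.

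**5. Would a baseline test reveal it?** With all 52 per arm at T0 the standard error is 15.44 × √(2/52) = 3.03. A two-sided 5% t test detects a 3-point difference about 17% of the time and a 5-point difference about 37%. A non-significant baseline test is therefore weak reassurance.

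**6. The group-by-time comparison.** Let the shift be b at T0 and b + c at T1. The between-arm difference in change is (b + c) − b = c. A stable shift (c = 0) cancels. Only selection that alters the course over time (c ≠ 0) biases this comparison. The documents do not allow c to be estimated.

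**The case against.** The case against has substance.

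- **There is more than one safeguard.** Letters go to every eligible diagnosed person, and sampling is consecutive. The Data analysis section plans baseline t tests and a mixed ANOVA that includes baseline. Setting and Data analysis provide adjustment where a sociodemographic variable differs. A reader might infer that a sociodemographic significance test is the only protection; the document does not support that.
- **The primary outcome is a comparison of changes.** The 13.5% and 29% therefore do not describe the group-by-time analysis. A reader might take them as the error rate of the primary comparison; they are not. The cross-sectional t tests at T1 and T2 are also planned, and the figures apply to those alone.
- **Centre differences are acknowledged.** Limitations does more than discuss generalisation. But differences between centre populations are not the same as enrolment that responds to a known programme, and the latter is not mentioned.
- **Two links are inferred.** No section says that local staff know their arm, or that the list precedes T0. The second inference is strong; the first rests on the briefing and the dissemination row. Nor does anything show that frailer patients actually decline the longer programme.
- **Little may remain to change.** Table 1 places the last letters in period 9, at the end of 2017, although Design describes recruitment and data collection as ongoing.

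These points narrow the concern without removing it. Neither disease stage nor motivation is among the named triggers for adjustment, and imbalance in either can alter trajectory.

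**Conclusion.** The concern holds as a design weakness. Arms are fixed before people are enrolled. Enrolment runs partly through staff who may know the programme, and the session list shows its length, probably before T0. Entry and early drop-out can therefore depend on arm, and Limitations does not recognise this as a threat to the comparison.

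No bias is shown to have occurred, and its size is unknown. For the unadjusted T1 and T2 t tests, assumed shifts of 3 and 5 points would raise false positives from 5% to about 13.5% and 29% (39 per arm, SD 15.44, clustering ignored). For the group-by-time comparison, a stable shift does no harm. The residual risk is imbalance in stage or motivation that changes the course of quality of life, which the planned measures do not address. The remedy is a low-cost improvement.

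**What to change.** **For any remaining wave**
- Have the eligibility interview done by the existing data-collection researchers, who are already kept unaware of allocation.
- Obtain consent and complete T0 before handing out the arm-specific session list.
- Keep people who then decline the sessions in the intention-to-treat set and seek their T1 and T2 questionnaires. The intervention section counts those attending fewer than 70% of sessions as lost to the study; state that this does not remove them from that set.

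**For all waves**
- Report numbers invited, eligible and enrolled, by centre and arm.
- In Limitations, name selection after allocation as a threat to the arm comparison, separately from generalisability and baseline centre differences.

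**Cost.** The first two changes reorder or reassign existing steps and need no new staff. Participants receive their session dates slightly later. Waves already recruited cannot be changed, so for those only the reporting and the Limitations text can help. A late change also makes procedure differ between waves, which should be reported.
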